|                                                 | 

- Measurements of height and weight

- To check the history of past/present illness, smoking/drinking, and resistance training

                                                                                                                                                                                                                                                                                                                                                                                                                                                                                                                                                                                                                                                                                                                                                                                                                                                                                                                                                                                                                                                                                                                                                                                                                                                                                                                                                                                                                                                                                                                                                                                                                                    |                          |                       |                          |                                       |              |                                                                                                                                                                                       |                                             |             |             |                                                 |             |             |

|  |                                                                                                                                                                                                                                                                                                                                                                                                                                                                                                                                                                                                                                                                                                                                                                                                                                                                                                                                                                                                                                                                                                                                                                                                                                                                                                                                                                                                                                                                                                                                                                                                                                                                                                                                                                                                                                                                                                                                                                                                                                                                                                                                                                                                                                                                                                                                                                                                                                                                                                                                                                                                                                                                                                                                                                                                                                 |
|--|---------------------------------------------------------------------------------------------------------------------------------------------------------------------------------------------------------------------------------------------------------------------------------------------------------------------------------------------------------------------------------------------------------------------------------------------------------------------------------------------------------------------------------------------------------------------------------------------------------------------------------------------------------------------------------------------------------------------------------------------------------------------------------------------------------------------------------------------------------------------------------------------------------------------------------------------------------------------------------------------------------------------------------------------------------------------------------------------------------------------------------------------------------------------------------------------------------------------------------------------------------------------------------------------------------------------------------------------------------------------------------------------------------------------------------------------------------------------------------------------------------------------------------------------------------------------------------------------------------------------------------------------------------------------------------------------------------------------------------------------------------------------------------------------------------------------------------------------------------------------------------------------------------------------------------------------------------------------------------------------------------------------------------------------------------------------------------------------------------------------------------------------------------------------------------------------------------------------------------------------------------------------------------------------------------------------------------------------------------------------------------------------------------------------------------------------------------------------------------------------------------------------------------------------------------------------------------------------------------------------------------------------------------------------------------------------------------------------------------------------------------------------------------------------------------------------------------|
|  | 
 
- To fill out Myers credibility index checking overall validity of informed consent document
 
- To fill out Acupuncture Belief Scale (ABS) and State-Trait Anxiety Inventory-X (STAI-X)
 
- To measure pressure pain phreshold (PPT) in the non-dominant upper arm
 
 
3. Induction of delayed onset muscle soreness model
 
 
- Measurement of 1 Repetition Maximum (1RM) in the non-dominant arm
 
- Repetitive arm-curl exercise in the non-dominant arm using 1RM weighted dumbbell
 
- Measurement of muscle discomfort in the non-dominant arm with visual analogue scale (VAS)
 
- Measurement of PPT in the non-dominant arm
 
 
4. Acupuncture treatment
 
 
- RA (PC2, LI4, LI11 and LU5 of the non-dominant arm) and PA (two points on the muscle belly of biceps brachii, 1 cun proximally from LI11, and 1 cun laterally from PC2 of the non-dominant arm) will be performed for 15 minutes once daily for three consecutive days with manipulation (by rotating 180 degrees clockwise and counter-clockwise in a frequency of 2 Hz at immediately, 3, 6, 9, and 12 minutes after needle insertion)
 
 
5. After acupuncture treatment
 
 
- To fill out de-qi questionnaire
 
- Measurement of muscle discomfort in the non-dominant arm with VAS
 
- Measurement of PPT in the non-dominant arm
 
 <hr/> 
1. Before acupuncture treatment
 
 
- Adverse event monitoring
 
- Measurement of muscle discomfort in the non-dominant arm with VAS
 
- Measurement of PPT in the non-dominant arm
 
 
2. Acupuncture treatment
 
 
- RA (PC2, LI4, LI11 and LU5 of the non-dominant arm) and PA (two points on the muscle belly of biceps brachii, 1 cun proximally from LI11, and 1 cun laterally from PC2 of the non-dominant arm) will be performed for 15 minutes once daily for three consecutive days with manipulation (by rotating 180 degrees clockwise and counter-clockwise in a frequency of 2 Hz at immediately, 3, 6, 9, and 12 minutes after needle insertion)
 
 
3. After acupuncture treatment
 
 
- To fill out de-qi questionnaire
 
- Measurement of muscle discomfort in the non-dominant arm with VAS
 
- Measurement of PPT in the non-dominant arm
 
 <hr/> 
1. Before acupuncture treatment
 
 
- Adverse event monitoring
 
- Measurement of muscle discomfort in the non-dominant arm with
 
 |
|--|---------------------------------------------------------------------------------------------------------------------------------------------------------------------------------------------------------------------------------------------------------------------------------------------------------------------------------------------------------------------------------------------------------------------------------------------------------------------------------------------------------------------------------------------------------------------------------------------------------------------------------------------------------------------------------------------------------------------------------------------------------------------------------------------------------------------------------------------------------------------------------------------------------------------------------------------------------------------------------------------------------------------------------------------------------------------------------------------------------------------------------------------------------------------------------------------------------------------------------------------------------------------------------------------------------------------------------------------------------------------------------------------------------------------------------------------------------------------------------------------------------------------------------------------------------------------------------------------------------------------------------------------------------------------------------------------------------------------------------------------------------------------------------------------------------------------------------------------------------------------------------------------------------------------------------------------------------------------------------------------------------------------------------------------------------------------------------------------------------------------------------------------------------------------------------------------------------------------------------------------------------------------------------------------------------------------------------------------------------------------------------------------------------------------------------------------------------------------------------------------------------------------------------------------------------------------------------------------------------------------------------------------------------------------------------------------------------------------------------------------------------------------------------------------------------------------------------|

|                            |                                                                                                                                                                                                                                                                                                                                                                                                                                                                                                                                                                                                                                                                                                                                                                                                                                                                                                                                                                                                                                                                                                                                                                                                                                                                                                                                                                                                                                                                                                                                                                                |
|----------------------------|--------------------------------------------------------------------------------------------------------------------------------------------------------------------------------------------------------------------------------------------------------------------------------------------------------------------------------------------------------------------------------------------------------------------------------------------------------------------------------------------------------------------------------------------------------------------------------------------------------------------------------------------------------------------------------------------------------------------------------------------------------------------------------------------------------------------------------------------------------------------------------------------------------------------------------------------------------------------------------------------------------------------------------------------------------------------------------------------------------------------------------------------------------------------------------------------------------------------------------------------------------------------------------------------------------------------------------------------------------------------------------------------------------------------------------------------------------------------------------------------------------------------------------------------------------------------------------|
|                            | 
VAS
 
 
- Measurement of PPT in the non-dominant arm
 
 
2. Acupuncture treatment
 
 
- RA (PC2, LI4, LI11 and LU5 of the non-dominant arm) and PA (two points on the muscle belly of biceps brachii, 1 cun proximally from LI11, and 1 cun laterally from PC2 of the non-dominant arm) will be performed for 15 minutes once daily for three consecutive days with manipulation (by rotating 180 degrees clockwise and counter-clockwise in a frequency of 2 Hz at immediately, 3, 6, 9, and 12 minutes after needle insertion)
 
 
3. After acupuncture treatment
 
 
- To fill out de-qi questionnaire
 
- Measurement of muscle discomfort in the non-dominant arm with VAS
 
- Measurement of PPT in the non-dominant arm
 
- To fill out acupuncture credibility Test
 
- Assessment of blinding effectiveness
 
 
4. Debriefing
 
 
- Debriefing to the type of acupuncture and informed consent form and interviewing about the other type of informed consent form
 
- Debriefing to the genuine study hypothesis and asking to participants whether the study design is acceptable and whether they can provide informed consent about the genuine study design and analysis their data
 
- Data of participants who decided not to provide written informed consent at the end of the study will not be analyzed.
 
 |
| 1.4.3 Main outcomes | 
Main outcomes are pain outcomes and blinding of participants
 
 
- Pain outcomes: PPT and VAS.
 
✓ Two way ANOVA is considered as the way of statistical plan as it can analyze the effect of two interventions (acupuncture and informed consent)
 
✓ The effect will be assessed as statistically significant when p value is under 0.05.
 
- Blinding of participants will be analyzed using a Blinding Index (BI, Bang, 2004).
 
                                                                                                                                                                                                                                                                                                                                                                                                                                                                                                                                                                                                                                                                                                                                                                                                                                                                                                                                                                                                                                                                   |

I submit this study protocol to Institutional Review Board of Kyung Hee University.

Date: 2019/07/31

Primary investigator: [name]

[figure not shown]

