|                                                                                           | 
 
• Response to withdrawal plausible (pharmacologically, pathologically)
 
• Event definitive pharmacologically or phenomenologically (i.e. an objective and specific medical disorder or a recognised pharmacological phenomenon)
 
• Rechallenge satisfactory, if necessary
 
√ Probable/Likely
 
• Event or laboratory test abnormality, with reasonable time relationship to drug intake
 
• Unlikely to be attributed to disease or other drugs
 
• Response to withdrawal clinically reasonable
 
• Rechallenge not required
 
√ Possible
 
• Event or laboratory test abnormality, with reasonable time relationship to drug intake
 
• Could also be explained by disease or other drugs
 
• Information on drug withdrawal may be lacking or unclear
 
√ Unlikely
 
• Event or laboratory test abnormality, with a time to drug intake that makes a relationship improbable (but not impossible)
 
• Disease or other drugs provide plausible explanations
 
√ Conditional/Unclassified
 
• Event or laboratory test abnormality
 
• More data for proper assessment needed, or
 
• Additional data under examination
 
√ Unassessable/Unclassifiable
 
• Report suggesting an adverse reaction
 
• Cannot be judged because information is insufficient or contradictory
 
• Data cannot be supplemented or verified
 
 
- Reporting of adverse events: adverse events will be analyzed by the investigator who will be in charge of examining the reaction suspected of the correlation with the treatment, abnormalities in the laboratory test results, and the frequency of serious adverse events occurrence. The collected safety data will be appropriately documented. All serious adverse events will be descriptively written. Adverse events will be collected through the patient's symptom report and investigator's observation and monitoring.
 |

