|  | 
 
3. Induction of delayed onset muscle soreness model
 
 
- Measurement of 1RM in the non-dominant arm
 
- Repetitive arm-curl exercise in the non-dominant arm using 1RM weighted dumbbell
 
- Measurement of muscle discomfort in the non-dominant arm with VAS
 
- Measurement of PPT in the non-dominant arm
 
 
4. Acupuncture treatment
 
 
- RA (PC2, LI4, LI11 and LU5 of the non-dominant arm) and PA (two points on the muscle belly of biceps brachii, 1 cun proximally from LI11, and 1 cun laterally from PC2 of the non-dominant arm) will be performed for 15 minutes once daily for three consecutive days with manipulation (by rotating 180 degrees clockwise and counter-clockwise in a frequency of 2 Hz at immediately, 3, 6, 9, and 12 minutes after needle insertion)
 
 
5. After acupuncture treatment
 
 
- To fill out de-qi questionnaire
 
- Measurement of muscle discomfort in the non-dominant arm with VAS
 
- Measurement of PPT in the non-dominant arm
 
 
 <hr/> 
 
1. Before acupuncture treatment
 
 
- Adverse event monitoring
 
- Measurement of muscle discomfort in the non-dominant arm with VAS
 
- Measurement of PPT in the non-dominant arm
 
 
2. Acupuncture treatment
 
 
- RA (PC2, LI4, LI11 and LU5 of the non-dominant arm) and PA (two points on the muscle belly of biceps brachii, 1 cun proximally from LI11, and 1 cun laterally from PC2 of the non-dominant arm) will be performed for 15 minutes once daily for three consecutive days with manipulation (by rotating 180 degrees clockwise and counter-clockwise in a frequency of 2 Hz at immediately, 3, 6, 9, and 12 minutes after needle insertion)
 
 
3. After acupuncture treatment
 
 
- To fill out de-qi questionnaire
 
- Measurement of muscle discomfort in the non-dominant arm with VAS
 
- Measurement of PPT in the non-dominant arm
 
 
 <hr/> 
 
1. Before acupuncture treatment
 
 
- Adverse event monitoring
 
- Measurement of muscle discomfort in the non-dominant arm with VAS
 
- Measurement of PPT in the non-dominant arm
 
 
2. Acupuncture treatment
 
 
- RA (PC2, LI4, LI11 and LU5 of the non-dominant arm) and PA (two points on the muscle belly of biceps brachii, 1 cun proximally from LI11, and 1 cun laterally from PC2 of the non-dominant arm) will be performed for 15 minutes once daily
 
 
 |

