| 2.3.5 Random sequence generation, allocation concealment, and blinding | 
 
■ Randomization 
 
- Random sequence generation
 
✓ The random sequence will be generated using Microsoft's Excel 2016 version.
 
- Allocation concealment
 
✓ Randomization of participants is carried out by a separate researcher who will not be related with other study procedures, and the random sequence will be placed in an opaque and sealed envelope so that identification of the sequence is not available.
 
 
 
■ Blinding 
 
- Blinding of participants
 
✓ Participants cannot discriminate two acupuncture, i.e., RA and PA, because appearance of PA is similar to that of RA (Park, 1999).
 
- Blinding of practitioner and outcome assessment
 
✓ Blinding of practitioner is not available considering the nature of intervention (acupuncture) and blinding of outcome assessment (PPT and VAS) will be achieved in that a separate researcher (not the practitioner) will measure the outcomes
 
 
 
                     |      |         |                          |                                                                                                                                                            |

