| 2.                         | Details of needling                                                                                                                                                                                                                                                                                                                                                    | 2a) Number of needle insertions per subject per session: four needles
2b) PC2, LU5, LI11, and LI4 in the non-dominant arm
2c) Depth of insertion: 10-20mm
2e) Needle stimulation: manual
2f) Needle retention time: 15 minutes
2g) Needle type: 0.25X40mm stainless-steel needle (Dongbang, Korea)                                                                                                                                                                                                                                                                                                                                                                                                                                                                                                                                                                                         |      |         |                            |                                                                                                                                                                       |                        |                                                                                                                                                                                                                                                                                                                                                                        |                      |                                                                                                                                             |

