| 2.3.10 Safety securing | 
 
- Monitoring adverse events
 
- Interviewing with participants at day 2 and day 3 visit
 
- Any adverse event will be described with details and numbers of adverse events have causal relationship or do not have one will be also described.
 
- Adverse events that are frequently reported following acupuncture: bruising, local pain, and minor bleeding (MacPherson, 2001)
 
- Adverse events refer to undesired and unintended signs (e.g., abnormalities in laboratory tests), symptoms, or diseases occurring after the treatment in the study. The events do not necessarily have a causal relationship with the treatment.
 
- Assessment of the severity (following Common Terminology Criteria for Adverse Events, CTCAE) 
 
✓ Grade 1 Mild; asymptomatic or mild symptoms; clinical or diagnostic observations only; intervention not indicated.
 
✓ Grade 2 Moderate; minimal, local or noninvasive intervention indicated; limiting age appropriate instrumental ADL*.
 
✓ Grade 3 Severe or medically significant but not immediately life-threatening; hospitalization or prolongation of hospitalization indicated; disabling; limiting self care ADL**.
 
✓ Grade 4 Life-threatening consequences; urgent intervention indicated.
 
✓ Grade 5 Death related to adverse event.
 
 
 
- Assessment of the causality (following WHO-UMC Causality Categories) 
 
✓ Certain
 
 
 
 |

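### On Days 2 and 3 the adverse-event interview is listed ahead of VAS and PPT, so it may colour the only pain readings after the first treatment that are not taken straight after needling

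*Protocol*

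**What the plan says.** Sections 1.4.2 and 2.3.4 give the same order for Days 2 and 3. Within the step before needling, "Adverse event monitoring" comes first, then "Measurement of muscle discomfort in the non-dominant arm with VAS", then PPT in the same arm.

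Section 2.3.10 sets the form of the monitoring: "Interviewing with participants at day 2 and day 3 visit". It also lists what is to be expected: "Adverse events that are frequently reported following acupuncture: bruising, local pain, and minor bleeding".

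Section 2.2.9 says how the events are gathered: "Adverse events will be collected through the patient's symptom report and investigator's observation and monitoring". It does not say whether that investigator is also the person who measures pain.

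Section 2.3.5 states that the practitioner cannot be blinded. It rests the blinding of PPT and VAS on the fact that "a separate researcher (not the practitioner) will measure the outcomes".

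Section 2.3.6 gives, for real acupuncture, "2c) Depth of insertion: 10-20mm", and 0 mm for the Park sham needle. Sections 1.4.3 and 2.3.9 name PPT and VAS, together with participant blinding, as the main outcomes.

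**The concern.** A participant who has just been asked about needle after-effects in one arm is next asked to rate discomfort in that same arm. Penetrating needles are more likely than blunt ones to leave something to report, so any carry-over from the question to the rating need not be equal between needle types.

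It need not be equal between consent forms either. Only the full-disclosure form tells participants that the control needle leaves the skin unbroken. For them a bruise or a spot of blood is a clue to allocation, and the interview brings it to mind just before the pain rating. For partial-disclosure participants the same sign carries no such message. The trial studies how information shifts reported pain and blinding, so a prompt of this kind touches its own question.

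The second route runs through the assessor. The only safeguard stated is that the person measuring is not the practitioner. If that person conducts or overhears the interview, an answer about bleeding or bruising may reveal the needle type before PPT is read. An analysis plan cannot repair either effect afterwards, because both arise when the data are collected.

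**Working it through.** **The plan's own figure.** Section 2.2.4 aims for 80 participants and allows for 10% dropout: 80 / (1 - 0.10) = 88.9, rounded up to 89. This matches the stated 89. The point does not depend on it, except that 80 supplies the group sizes used below.

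**Counting the readings** (1.4.2 and 2.3.4):

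| Occasion | VAS | PPT | After first treatment? | Straight after needling? | Straight after adverse-event item? |
|---|---|---|---|---|---|
| Day 1, screening | no | yes | no | no | no |
| Day 1, after exercise | yes | yes | no | no | no |
| Day 1, after needling | yes | yes | yes | yes | no |
| Day 2, before needling | yes | yes | yes | no | yes |
| Day 2, after needling | yes | yes | yes | yes | no |
| Day 3, before needling | yes | yes | yes | no | yes |
| Day 3, after needling | yes | yes | yes | yes | no |

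- VAS is read 6 times and PPT 7 times. Readings not taken straight after needling: 3 for VAS and 4 for PPT.
- From the first treatment onward there are 5 readings of each: 3 straight after needling and 2 not.
- Both of those 2 stand directly below the adverse-event item.

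**Which contrasts could be affected.** Suppose prompting shifts the mean in the real-needle groups by *a* under full disclosure and *b* under partial disclosure, and leaves the placebo groups unchanged (a simplification). Then:

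- needle-type main effect: bias (a + b)/2
- disclosure main effect: bias (a - b)/2
- interaction (difference of differences): bias a - b

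If a = b, only the needle-type effect is biased, and the disclosure effect and interaction are untouched. If a differs from b, all three can be touched. The differing consent wording gives a reason why a and b might differ, but no value for either.

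**Illustration for the needle-type contrast.** Assumptions not in the document: equal allocation (40 real, 40 placebo), one pre-needling VAS tested two-sided at 0.05, no true effect, normal approximation, VAS SD of 20 mm, and a prompting shift of 2-5 mm in the real-needle groups.

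- Standardised shift: 2/20 = 0.10 SD to 5/20 = 0.25 SD.
- Standard error: sqrt(1/40 + 1/40) = sqrt(2/40) = 0.2236 SD.
- Rejection rate: 1 - Φ(1.96 - shift/SE) + Φ(-1.96 - shift/SE).
- Shift 0.10 SD: shift/SE = 0.447, rate 7.3%.
- Shift 0.25 SD: shift/SE = 1.118, rate 20.1%.

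Over a wider assumed range, shifts of 0.2, 0.3 and 0.5 SD give 14.5%, 26.9% and 60.9%.

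**The case against.** **The order is listed, not mandated.** The steps are numbered, but the items within a step are dashes. That is true. Still, both schedules list the same order and nothing directs staff otherwise, so it is the order they are likely to follow.

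**Other pain readings escape the interview.** A reader might infer that the two pre-needling readings are the only ones not taken straight after needling. They are not: Day 1 has PPT at screening, and VAS and PPT after exercise. The statement holds only for readings after the first treatment.

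**Nothing says the assessor is present.** This stands. A reader might infer that the assessor is unblinded, but section 2.2.9 names only the investigator and section 2.3.5 only a researcher other than the practitioner. The text neither places the assessor at the interview nor keeps the assessor away.

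**A common shift cancels from the disclosure contrasts.** This is correct, as the algebra shows. It leaves the needle-type contrast exposed, and it protects the disclosure contrasts only if prompting acts alike under both consent forms.

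**Direction is unknown.** Asking about needle-site pain first might help a participant separate it from muscle soreness, and real after-pain is present whether or not anyone asks. Both remarks stand.

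**Checking for harm at the start of a visit is sensible.** It is. The change below keeps the check ahead of any further needling.

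**Reordering is only a partial cure.** An interview held before needling still precedes that day's post-needling readings, and the Day 2 interview precedes all Day 3 readings. This stands, and it is why the fix also keeps the assessor out of hearing.

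**Text may be absent.** The section numbers at hand pass from 2.3.6 to 2.3.9. If the intervening sections settle the order or the interviewer, only the schedule needs to be brought into line.

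**Conclusion.** The point holds as a free improvement to the measurement order, not as a demonstrated bias. The documents establish the listed order in both schedules, the interview format, the 10-20 mm versus 0 mm difference in depth, and an assessor safeguard that says nothing about the interview. Two of the five post-treatment readings of each pain outcome are exposed to direct prompting, and they are the two that best show delayed soreness apart from immediate needle sensation.

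The size and direction of any bias cannot be derived. A reader might take 7-20% as the trial's actual false-positive rate. It is not: it follows only from the assumed 2-5 mm shift and 20 mm SD, and it concerns the needle-type contrast alone. An effect on the disclosure contrasts is possible, since only one consent form makes the needle signs informative, but it is unquantified.

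**What to change.** In sections 1.4.2 and 2.3.4, Days 2 and 3, step 1, list VAS and PPT first and adverse-event monitoring after them, still before that day's needling, and state that this order is to be followed. In section 2.3.10, state that someone other than the PPT/VAS assessor conducts the interview, out of the assessor's hearing. The practitioner, who is already unblinded, would serve.

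The VAS item should stay as it is. A reader might think of confining it to the exercised muscle so as to keep needle-site pain out, but two of the placebo points lie on the belly of the biceps, the muscle worked by the arm curls, so the rewording would not achieve that.

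The cost is a swap of lines in two schedules and one added sentence. No visit, measurement, staff or sample-size figure changes.
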